## Abstract

**Background:**

The purpose of this study is to evaluate whether wrapping of the pedicled falciform ligamentum flap around the gastroduodenal artery (GDA) stump/hepatic artery can significantly decrease the incidence of erosion hemorrhage after pancreatoduodenectomy (PD).

**Methods/design:**

This is a randomized controlled multicenter trial involving 400 patients undergoing PD. Patients will be randomized into two groups. The intervention group consists of 200 patients with a prophylactic wrapping of the GDA stump using the pedicled falciform ligament. The control group consists of 200 patients without the wrap. The primary endpoint is the rate of postoperative erosion hemorrhage of the GDA stump or hepatic artery within 3 months. The secondary endpoints are postpancreatectomy hemorrhage stratified according to the texture of the pancreas, postoperative pancreatic fistula (POPF), postoperative rate of therapeutic interventions, morbidity, and mortality.

**Discussion:**

Only few retrospective studies investigated the effectiveness of a falciform ligament wrap around the GDA for prevention of erosion hemorrhage. Erosion hemorrhage occurs in up to 6–9% of cases after PD and is most frequently evoked by a POPF. Erosion hemorrhage is associated with a remarkable mortality of over 30%. The rate of hemorrhage after performing the wrap is reported to be low. However, there exist no prospectively controlled data to support its general use. Therefore, the presented randomized controlled trial will provide clinically relevant evidence of the effectiveness of the wrap with statistical significance.

**Trial registration:**

clinicaltrials.gov, NCT02588066; Registered on 27 October 2015.

**Electronic supplementary material:**

The online version of this article (10.1186/s13063-018-2580-0) contains supplementary material, which is available to authorized users.

## Background

Pancreatoduodenectomy (PD) is the standard surgical procedure for malignant, benign, and borderline tumors (e.g., intraductal papillary mucinous neoplasms) of the pancreatic head and neck. Moreover, it is also indicated for some patients with chronic pancreatitis. Postoperative morbidity has been reduced by centralization at high-volume centers, advances in surgical techniques, and perioperative management but still ranges between 40 and 60% [1]. The most frequent surgical postoperative complications are development of a pancreatic fistula (POPF), delayed gastric emptying (DGE), and postpancreatectomy hemorrhage (PPH) [2]. The development of a POPF is one of the most complex complications after PD [3]. The incidence of POPF still ranges between 20 and 30% after pancreatic resections [4, 5]. The most serious sequela of an established POPF is the erosion of the gastroduodenal artery (GDA) stump by pancreatic juice or local inflammation, leading to delayed and potentially lethal PPH. Erosion hemorrhage occurs with the usual delay of a few days up to several weeks [6–8]. Late PPH is predominantly caused by erosion or pseudoaneurysm formation of the GDA or hepatic artery (HA) (>24 h after the index operation). According to the literature, the incidence ranges between 3 and 6% or even higher in single-center studies and is associated with a significantly increased mortality of 16–20% [7–9].

In recent years, technical efforts have been undertaken to lower the incidence of erosion hemorrhage or POPF, i.e., covering of either the skeletonized and divided arteries or the pancreatojejunostomy with the round or falciform ligament or with an omental flap [10]. A promising surgical technique for covering the GDA stump is to wrap the pedicled falciform ligament around the skeletonized HA and the GDA stump [11]. This procedure is frequently practiced in Asia, although its routine use lacks solid evidence and is rarely used in Europe or the United States [10]. There are no reports on randomized controlled trials investigating the prophylactic use of the pedicled falciform ligament for prevention of erosion hemorrhage [12]. For this reason, the presented randomized controlled multicenter trial was initiated to assess whether the use of the pedicled falciform ligament wrap can significantly decrease the incidence of postpancreatectomy erosion hemorrhage.

### Trial design and study setting

The title of this clinical trial is “Pancreatoduodenectomy with or without prophylactic falciform ligament wrap around the gastroduodenal artery stump for prevention of pancreatectomy hemorrhage” (Additional file 1). The study is designed as a randomized controlled, national (Germany) multicenter trial with an interventional group (A: PD operation with the creation of a pedicled falciform ligament wrap around the GDA stump) and a control group (B: PD operation without the ligament wrap). Participating centers are at least four German university centers and two academic centers, which are officially certified for pancreatic surgery (pancreatic cancer center). Immediate access to computed tomography (CT) and a 24-h availability of interventional radiology must be guaranteed. A list of participating centers can be obtained from the senior author by request.

### Aim of the study and study endpoints

The aim of the study is to evaluate whether a pedicled falciform ligament wrap can decrease erosion hemorrhage of the stump of the GDA in the presence of a POPF.

Therefore, the primary endpoint of the study is the rate of postoperative erosion hemorrhage from the GDA stump or the HA within 3 months from the index operation.

The secondary endpoints are:Incidence of late PPH (according to the International Study Group of Pancreatic Surgery (ISGPS) definition [13]) in the entire study population and divided into subgroups with soft and hard pancreatic texture (also depending on the underlying histopathology [e.g., cancer, cystic lesion, or chronic pancreatitis])Incidence of clinically relevant POPF (according to POPF grades B and C, ISGPS definition [3, 14])Incidence of symptomatic hepatic malperfusion and narrowing/stenosis of the HA (diagnosed by computed tomography or angiography)Postoperative rate of therapeutic interventions (computed tomography-guided drainage or angiographic studies)Reoperation ratePostoperative morbidity and mortality (during hospital stay and at 3 months postoperative)

Erosion hemorrhage from the GDA stump or the HA is defined as postoperative bleeding or pseudoaneurysm formation (proved by CT angiography, conventional angiography, or relaparotomy) from the GDA stump or the HA within 3 months from the index operation. Clinically relevant POPF grade C is defined as POPF, which is causative for a reoperation, organ failure, or death of the patient [14].

### Study population (inclusion and exclusion criteria)

The targeted study population includes all patients scheduled for elective open PD (Whipple or pylorus-preserving) with reconstruction using a pancreatojejunostomy (anastomosis of the pancreas to the jejunum) in cases of tumors or cystic lesions of the pancreatic head, the distal bile duct, and the duodenum or in cases of chronic pancreatitis. Further inclusion criteria are as follows: male and female patients, age equal to or older than 18 years, American Society of Anesthesiologists (ASA) score I–III, and a completed written informed consent form. Exclusion criteria are as follows: potential conditions/circumstances after previous abdominal surgery with resection of the falciform ligament (e.g., status post liver resection), no creation of a pancreatojejunostomy (e.g., pancreatogastrostomy, total pancreatectomy, or non-resectability), and simultaneous arterial resection or reconstruction (e.g., hepatic or splenic, or superior mesenteric artery).

### Surgical technique

The standard technique of PD and surgical instruments may vary in several aspects. The technique and critical steps of the own Dresden center were described elsewhere [15].

The following operation steps are crucial for the trial evaluation and are predefined for patients in both the intervention and control arms:The abdominal incision can be either a midline laparotomy or a transverse subcostal incision.After opening the abdominal cavity, attention should be paid to preserve the round and falciform ligament over its entire length, before division near the umbilicus and separation from the ventral abdominal wall.Preparation of the falciform ligament (see also [12]): The falciform ligament is then further dissected from the ventral abdominal cephalad along the ventral attachment. At the junction to the coronary ligament, the falciform ligament is freed from the ventral hepatic surface until the round ligament is reached. This technique results in a pedicled falciform ligament, with the round ligament being the pedicle.When dividing the GDA, the stump of the GDA should be kept as long as possible. Division of the GDA is performed using a suture stitch (Prolene 4-0) and two titanium clips as a standard. Other deviating techniques of dividing the GDA are allowed according to the protocol but should be recorded in the case report form (CRF).Reconstruction is achieved by an end-to-side pancreatojejunostomy. The technique of this type of anastomosis is at the discretion of the surgeon.A resection of the portal vein can be performed if necessary and is no exclusion criterion.Intra-abdominal drains can be placed after completion of the operation.

For patients in the intervention group, the technique for creation of the pedicled falciform ligament wrap as it should be performed in this trial is as follows: After completion of the pancreatic, bile duct, or gastric/duodenal anastomosis, the prepared pedicled falciform ligament is carefully tunneled below the common HA and wrapped around the GDA stump in a tension-free fashion using only one turn. Fixation is then performed with two to three stitches using polydioxanone (PDS) 5-0. The last step is to ensure a proper pulsation of the HA after completion of the wrap. The covering of the divided and skeletonized arteries (GDA stump, hepatic artery) by the pedicled falciform ligament patch is a quick and safe surgical procedure for experienced pancreatic surgeons.

### Randomization

Patients will be screened for eligibility considering the inclusion criteria (see above) on the day of admission (usually the day before the surgery). After obtaining the written informed consent, the randomization will be performed intraoperatively after proving the exclusion criteria. The randomization is designed as block randomization (via envelopes), with fixed block sizes in a 1:1 allocation ratio. The envelopes were prepared by an authorized trial coordinator at the center in Dresden and distributed to the participating sites as needed. It is mandatory to check all eligibility criteria before opening of a randomization envelope by authorized trial personnel only. The investigator has to consecutively assign the envelopes to the patients. He is requested to document the assignment carefully in the patient identification log.

The details of the randomization will be kept safe and confidential. Subjects withdrawn from the trial retain their identification codes (e.g., randomization number). New subjects receive a new identification code.

The randomization sequence was generated using the established R statistics software package (R version 3.1.3, the R Foundation for Statistical Computing). The block size will be kept confidential until completion of recruitment. Eligible patients will be randomized intraoperatively to one of the two groups (control group or intervention group) after the surgeon has confirmed resectability and the availability of the pedicled falciform ligament. In cases when exclusion criteria (e.g., no performance of a pancreatojejunostomy or total pancreatectomy) are met after randomization, the respective patients were withdrawn from the trial.

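### A fixed block size, in site-held envelopes opened in order by an unblinded surgical team, leaves some upcoming allocations predictable; randomly varying sizes would remove most of that certainty.

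*Protocol article*

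**What the plan says.** All of the allocation procedure is in the Randomization section of the protocol article.

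- Scheme: "The randomization is designed as block randomization (via envelopes), with fixed block sizes in a 1:1 allocation ratio". The section later refers to a single block size, so one constant size is the natural reading.
- Custody: a trial coordinator in Dresden prepares the envelopes, and they are "distributed to the participating sites as needed".
- Order and record: "The investigator has to consecutively assign the envelopes to the patients", and "He is requested to document the assignment carefully in the patient identification log".
- Timing: randomization takes place during the operation, "after the surgeon has confirmed resectability and the availability of the pedicled falciform ligament".
- Safeguards: "The block size will be kept confidential until completion of recruitment". The other randomization details are also confidential, and authorized personnel must check all eligibility criteria before opening an envelope.

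The Surgical technique section shows that the allocation is visible to those who carry it out. In the intervention group, "the prepared pedicled falciform ligament is carefully tunneled below the common HA and wrapped around the GDA stump"; in the control group this step is absent.

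**The concern.** Concealment depends on the person who decides on entry not knowing the next arm. Here five stated features work against that together: a constant block size, envelopes at the site, use in sequence, a local record of earlier assignments, and a team that cannot be blinded. The final confirmation before opening is made by a member of that team.

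Confidentiality of the block size helps but is partial. With at least six centers, 400 patients average up to about 67 per center. That is some 8 to 17 consecutive blocks of size 8 to 4, enough for a regular pattern of balance to show.

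A team that can tell which arm comes next may, knowingly or not, judge a borderline patient differently. The primary endpoint is rare, so a few such decisions could affect the comparison.

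**Working it through.** **The plan's own figures.** The article gives no figure for predictability and does not disclose the block size. Its sample size reproduces: the exact two-sided Fisher test at 6.4% versus 0.7% has 80.0% power with 174 per group (79.7% with 173), and 174 / 0.87 = 200 per group. This point does not affect it.

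**Assumption.** The block size is B = 2m, shown for the usual values. The observer knows B, knows where blocks start, and knows every earlier allocation at the site.

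**Allocations known with certainty.** Once one arm has used up its m places, the rest of the block is determined. For B = 4 there are six equally likely sequences. Three are AABB (last 2 known), ABAB (last 1) and ABBA (last 1), and the other three are their mirror images. The mean is (2 + 1 + 1) / 3 = 4/3 per block, and (4/3) / 4 = 1/3. In general the expected number is 2m / (m + 1) per block, a share of 1 / (m + 1). The last column is the share guessed correctly by always naming the arm with more places left; chance is 50%.

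| Block size | Known with certainty | Upper bound out of 400 | Best guess correct |
|---|---|---|---|
| 4 | 1/3 = 33% | 133 | 71% |
| 6 | 1/4 = 25% | 100 | 68% |
| 8 | 1/5 = 20% | 80 | 67% |
| 10 | 1/6 = 17% | 67 | 65% |

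**If blocks are not whole within a site.** In a simulation of blocks of 4 dealt to six sites in packs of 5 or 10, predictions that the observer would take as certain were right only about 65% and 76% of the time. The shares in the table are therefore maxima.

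**Events expected at the design rates.**
- 174 per group: 174 × 0.064 + 174 × 0.007 = 11.1 + 1.2 = 12.4.
- 200 per group: 200 × 0.064 + 200 × 0.007 = 12.8 + 1.4 = 14.2.

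**Sensitivity of the primary test (two-sided Fisher, 174 per group).**
- 1 versus 11, close to the planned result: p = 0.0055. With one event fewer in the control group (1 versus 10), p = 0.0105.
- 1 versus 8: p = 0.037. 1 versus 7: p = 0.067.

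One event does not turn the planned result. It would turn a result nearer the boundary.

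**Effect of varying block sizes.** This was simulated with 67 patients per site and a guesser who knows the set of sizes but not the size of the current block.

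| Block sizes | Known with certainty | Best guess correct |
|---|---|---|
| Fixed 4 | 32% | 70% |
| 4 and 6 | 6% | 69% |
| 4, 6 and 8 | 2% | 68% |

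(The fixed-4 row is slightly below 33% because 67 is not a multiple of 4.)

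**The case against.** The case on the other side has real force.

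- **The shares are maxima.** They need an observer who knows the size, the block starts and the full site history from the first patient. The size is confidential and would have to be inferred while recruitment runs. Several surgeons may operate at one center, and the article does not say that the operating surgeon reads the log. This stands, so the figures are given only as upper bounds.
- **Steering is not easy.** A reader might infer that surgeons could freely direct high-risk glands to one arm. The documents do not support that. Neither pancreatic texture nor fistula risk is an entry criterion, most exclusions are concrete, and the ligament is prepared in both arms. Steering would require misreporting resectability or ligament availability. This stands.
- **Distribution to sites.** A reader might take on-demand distribution as a further fault because it may split blocks. The article does not say whether blocks are kept whole, and may leave that to the full protocol. Split blocks would also lower local predictability, so this cannot be added to the maximum shares. It is not part of the point.
- **The remedy is partial.** Varying sizes hardly changes best-guess accuracy. This stands and is stated with the fix.

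None of this answers the central matter. A constant size is a stated choice, and in this setting it is weaker than a readily available alternative.

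**Conclusion.** The point holds as an inexpensive improvement to concealment. The fixed block size is stated outright, so this does not rest on a detail that the article leaves out. Under the least favorable assumptions, 20% to 33% of allocations could be known in advance for blocks of 8 to 4. The true share is lower if blocks are split across sites, if the surgeon sees only part of the sequence, or until the size has been inferred.

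Two stronger readings should be resisted. One is that allocation has been subverted or the result biased; nothing in the article shows this. The other is that a single steered patient would decide the trial; at the planned rates the result is about 1 versus 11 events, and one event does not move it across 0.05. What remains is that 12 to 14 expected events leave limited room for selective entry, and that confidentiality of a constant size is only partial protection.

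**What to change.** For all envelopes not yet issued or opened, replace the fixed block size with randomly varying sizes (for example 4, 6 and 8), generated as a separate list for each center. Keep the set of sizes confidential, as is now done for the single size. Require the patient code and the confirmation of all eligibility criteria to be written on the envelope before it is opened. The two parts belong together: separate lists keep blocks whole within a center, which with a constant size would leave local predictability at its maximum.

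This brings certain predictions down to about 2% but leaves best-guess accuracy near 68%, so it removes most certainty and not all guessing.

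The programming is a few lines of R, which the trial already uses. The practical cost is that recruitment has been open since July 2016: unused envelopes must be recalled from the centers and reprinted, possibly with a minor amendment. Sample size, endpoint, analysis and surgical technique are unchanged.

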## Discussion

The clinical trial is the first randomized controlled study to investigate the effectiveness of a pedicled falciform ligament wrap for prevention of postpancreatectomy erosion hemorrhage. Creation of a falciform ligament wrap is a simple surgical technique with low associated morbidity. In the past, the falciform ligament has been used in hepatic injury [18] or for perforated duodenal ulcer [19]. More recently, it has been assessed for prevention of POPF after distal pancreatic resections [20]. The latter technique is at present analyzed by the randomized, controlled “DISCOVER” trial [21].

Compared with POPF, delayed erosion hemorrhage occurs less frequently but carries a high mortality [22]. The substantial mortality is closely related to the incidence of a POPF, formation of a pseudoaneurysm, delayed PPH, and soft pancreatic tissue [23]. Furthermore, pseudoaneurysm formation of the visceral vessels may be favored by the radicality of vascular dissection and lymphadenectomy, as well as by the length and closure of the GDA stump.

Before initiating the present trial, we performed a retrospective analysis of our own experience in using the pedicled falciform ligament wrap for patients undergoing PD. The study confirmed the high mortality of erosion hemorrhage (39%) and the feasibility of the technique. However, only 39 patients with the wrap were retrospectively identified, and the difference compared with cases without the wrap was not significant [12]. We then continued with a systematic literature review and found that the overall reported rate of erosion hemorrhage after PD and pedicled falciform ligament wrap is low (0.9%). In comparison, the median rate of erosion hemorrhage in studies which reported outcomes of PDs without the use of a wrap was 4.1 (interquartile range, 3.7–4.7) [8, 9, 23, 24].

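### The envelope may be opened before reconstruction, so eligibility can be settled after allocation, against the protocol's own pre-opening check and its intention-to-treat analysis, and the surgeon can know the arm while choosing the anastomosis

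*Protocol article*

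**What the plan says.** All of this is in the protocol article.

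- **Timing of allocation (Randomization).** "Eligible patients will be randomized intraoperatively to one of the two groups (control group or intervention group) after the surgeon has confirmed resectability". The sentence goes on to a second condition, so that the full trigger is "after the surgeon has confirmed resectability and the availability of the pedicled falciform ligament".
- **Eligibility check (Randomization).** Every criterion must be checked before an envelope is opened.
- **Withdrawal (Randomization).** Randomized patients later found to meet an exclusion criterion are withdrawn. The examples are a missing pancreatojejunostomy and a total pancreatectomy.
- **Exclusion criterion (Study population).** Patients in whom no pancreatojejunostomy is made are excluded. The examples are pancreatogastrostomy, total pancreatectomy and non-resectability.
- **Common steps (Surgical technique).** Ligament preparation, GDA division and reconstruction "are predefined for patients in both the intervention and control arms".
- **The differing step (Surgical technique).** "After completion of the pancreatic, bile duct, or gastric/duodenal anastomosis, the prepared pedicled falciform ligament is carefully tunneled below the common HA" and wrapped, in the intervention arm only.
- **Discretion (Surgical technique).** For the pancreatojejunostomy: "The technique of this type of anastomosis is at the discretion of the surgeon". GDA closure has a standard method, but other methods are permitted if recorded. Stump length has a direction (long) but no fixed value.
- **Recording (Data monitoring and quality assurance).** The intraoperative case report form (CRF) captures stump length (below 8 mm, or 8 mm and above) and whether closure followed the protocol.
- **Prognostic factors (Discussion).** Pseudoaneurysm formation may be favored by the extent of vascular dissection, "as well as by the length and closure of the GDA stump".
- **Analysis (Statistical considerations).** Both intention-to-treat and per-protocol analyses are planned.

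**The concern.** The arms differ in one late step, and the ligament is prepared in every patient. Nothing in the article requires the arm to be known before that step, yet the stated trigger for opening the envelope comes earlier. Two things follow.

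First, a patient's place in the trial can depend on a decision taken after allocation. Excluding randomized patients is harmless only when the exclusion could not have been influenced by the arm. Whether a pancreatojejunostomy is made is a surgeon's decision, and here it can be made with the arm known. Withdrawing such patients undermines the comparison that an intention-to-treat analysis is meant to protect.

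Second, an operator who knows the arm still has technical choices to make. The article itself links some of them, stump length and closure, to pseudoaneurysm, which counts as a primary endpoint event.

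**Working it through.** **1. Can allocation precede reconstruction?** Yes. A patient can be withdrawn after randomization for lack of a pancreatojejunostomy only if the envelope was opened before the pancreatojejunostomy was made. Of the three examples under that criterion, non-resectability is settled by the stated trigger. The other two, pancreatogastrostomy and total pancreatectomy, are not.

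**2. Do the rules fit together?** No. The pancreatojejunostomy criterion is certain only at reconstruction. If all criteria are truly checked before opening, the withdrawal sentence has nothing to act on for this criterion. If the withdrawal sentence is needed, the check was not complete. The article also does not say how patients withdrawn from the trial enter the intention-to-treat set.

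**3. Which choices can be made with the arm known?**

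| Choice | Left open by the text? | After allocation? |
|---|---|---|
| Pancreatojejunostomy technique | Yes, surgeon's discretion | Yes, by step 1 |
| GDA closure | Partly: standard method, deviations allowed | Not stated |
| GDA stump length | Partly: direction given, no fixed length | Not stated |
| Drains | Yes, optional | Yes, placed at the end |

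**4. The plan's own figure.** Inputs from Statistical considerations: 6.4% against 0.7%, two-sided Fisher exact test, alpha 0.05, 80% power, 13% drop-out.

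Power(n) = Σ Bin(x; n, 0.064) × Bin(y; n, 0.007), summed over all tables (x, y) with Fisher p < 0.05.

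- n = 173 gives 79.70% and n = 174 gives 80.01%, so 174 per group is reproduced.
- 174 / (1 − 0.13) = 200 per group, 400 in total. The allowance is 200 − 174 = 26 per group.

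**5. Where withdrawals enter.** They draw on the same allowance. The loss rates below are assumptions, apart from the planned 13%:

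| Loss from 200 per group | Analyzed per group | Power |
|---|---|---|
| 0% | 200 | 86.7% |
| 2% | 196 | 85.8% |
| 5% | 190 | 84.4% |
| 10% | 180 | 81.8% |
| 13% | 174 | 80.0% |
| 15% | 170 | 78.8% |
| 20% | 160 | 75.3% |

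The share of the 13% due to missing pancreatojejunostomies is not given, so no row can be assigned to the present timing or to a later one.

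**6. Sensitivity to arm-aware technique, with assumed rates.** Suppose the wrap did nothing, but other differences in technique lowered the wrap-arm rate from 6.4%. With 174 per group, the test would be significant in 7.8% of trials at 4.5%, 11.4% at 4.0% and 23.3% at 3.0%, against 2.9% with no difference. These figures show how the test would respond. They do not estimate what will happen.

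**The case against.** The best defense is that the Randomization section does not allow opening at any moment after resectability. It also requires the exclusion criteria to be ruled out first, and a missing pancreatojejunostomy is one of them. On that reading opening is meant to be late, and the withdrawal sentence covers rare failures. This stands in part. It makes the problem an inconsistency to be reconciled rather than an unrestricted early opening. It does not remove the problem, because the text foresees such failures and resolves them by removing randomized patients.

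A reader might infer more than the article supports in four ways.

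- **That the surgeon knows the arm when dividing the GDA.** The article does not place GDA division relative to the envelope. Only knowledge before the pancreatojejunostomy is established, so the stump argument is conditional.
- **That stump technique is uncontrolled.** A standard closure is predefined for both arms, and "Other deviating techniques of dividing the GDA are allowed according to the protocol but should be recorded in the case report form (CRF"). Stump length and closure type are captured. These records can reveal an imbalance but cannot prevent one, and an entry made after allocation does not show that the choice was made without knowledge of the arm.
- **That later opening would raise power to 86.7%.** That needs all of the 13% loss to come from these withdrawals. Losses before the 3-month visit would remain whatever the timing.
- **That the bias favors the wrap.** A surgeon who knows that the patient is a control could take more care, which would pull the result toward no effect.

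**Conclusion.** The point holds as a flaw in the stated randomization rule, and it should be corrected. The text firmly supports two parts. Allocation can precede reconstruction, so eligibility may be settled with the arm known, in conflict with the pre-opening check and the intention-to-treat analysis. The anastomosis technique can also be chosen with the arm known. A third part, stump length and closure, depends on opening before GDA division, which the article leaves open.

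The size is unknown. The article gives neither the number of such withdrawals nor a basis for the amount or direction of bias. The sample size of 174 per group and 400 in total is reproduced and does not change. Power stays at or above 80% while total loss does not exceed 13%.

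**What to change.** Amend the Randomization section for all remaining patients:

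- Open the envelope only after the GDA has been divided and the pancreatojejunostomy completed, immediately before the point in the existing operative sequence at which the wrap would be made. Do not tie opening to completion of every anastomosis. The Surgical technique section joins the anastomoses with an or, so it does not establish that all of them precede the wrap, and the operative sequence should not change for the sake of randomization. If any center makes the wrap before the pancreatojejunostomy, the investigators need to reconcile that wording.
- Enter stump length, closure type and anastomosis technique in the CRF before opening. The first two are already collected, so what changes for them is the timing.
- Reconcile the eligibility-check and withdrawal sentences with this rule.
- Keep patients already randomized in the intention-to-treat set, or report their withdrawals by arm with reasons.

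The cost is a short amendment and a note to sites. No operative step is added, because the ligament is prepared in both arms. Recruitment is under way, so the trial will contain two randomization timings, and this should be reported. The change does not protect drain placement or postoperative care, which come after allocation in any case.
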